### 9.5 Evaluation of vestibular function

A recent study found that the prevalence of vestibular disorders such as vertigo and dizziness was 15-20% in adults. In addition, studies suggest that some breast cancer treatments have effects on vestibular function.

The vHIT (Vestibular Head Impulse Test) is a rapid, non-invasive test for objective assessment of vestibular function, and more specifically of each of the six semicircular canals individually. It is generally used to detect possible vestibular dysfunctions as part of the assessment of vertigo and balance disorders.

During the test, a helmet is placed on the participant's head, with micro-cameras recording eye movement. The operator will manually apply rapid head movements in different directions. During the movement, the helmet will record both head and eye movements. From this data, the physician will be able to assess whether vestibular function is intact or affected, and what the condition is, if any.

## 10 GALVANIC VESTIBULAR STIMULATION (GVS)

### 10.1 Description of the technique

The GVS principle is based on the use of two electrodes included in the stimulation helmet, a cathode (negative) and an anode (positive) placed on the right and left mastoid bones, behind the ears. The first has an excitatory role, while the second has an inhibitory one.

| Session 1 - Day 1                                                                                                                                    | Session 2 - Day 2                                                                                                                                                                                                               |
|------------------------------------------------------------------------------------------------------------------------------------------------------|---------------------------------------------------------------------------------------------------------------------------------------------------------------------------------------------------------------------------------|
| 

- BDI-II

- BPI

- STAI - State

- STAI - Trait

- PCL-5 (patients only)

 | 

- PSS

- Modified dispositional brief-COPE (before suspicion of cancer) (patients only, T1 only)

- Dispositional COPE Brief

- PTGI

- IPAQ

 |

**Figure 7.** Questionnaires proposed during the 2 evaluation sessions

Note: the KSS is offered at the beginning and end of each assessment day, i.e. a total of 4 times.

A direct electric current is passed through these electrodes to stimulate the irregular fibres of the vestibulocochlear nerve . Sponges that have been soaked in a saline solution will be positioned at the electrodes' location, for better contact with the skin. Electric power intensity will be 1mA .

A stimulation headset (**Erreur ! Source du renvoi introuvable.**), already used in other protocols carried out in the COMETE unit, will be made available to participants at time T2 of the study. This headset, marketed by Soterix, is CE-marked and delivers vestibular stimulation defined by the experimenter in a pre-regulated, pre-programmed way. Participants will be briefed on the principle of use, and will be able to familiarize themselves with its operation before taking the equipment home. In addition, participants will already have been familiarized with the video-conferencing platform at the University of Caen during T1.

During the 2 weeks of stimulation, participants will receive an email reminding them of their appointment via the video-conferencing platform. They will then be able to connect at the given time (in the morning, around 9:30 a.m.) and will be in visual contact with one of the team's experimenters, who will check that the headset is correctly positioned and will be able to talk to the participant. The stimulation system is pre-programmed and cannot be modified unless you have a specific code known only to the research team. Once the position of the headset and sponges has been checked, stimulation will be performed for 20 minutes, during which time the participants will be seated and remain in contact with the team. At the end of the 20 minutes, three visual analog scales for pain, fatigue and well-being will be offered.

[figure not shown]

**Figure 8** All the equipment required for vestibular stimulation, including the device for controlled, pre-programmed delivery of the stimulation protocol, the headset and the individually delivered sponges.

## 10.2 Contraindications and expected side effects

GVS induces oculomotor (i.e. nystagmus), postural and perceptual (e.g. head turning) responses. However, the responses observed depend on the type of stimulation, the electrodes, the individual and the context. Some individuals feel mainly perceptions of canalicular origin (i.e. rotation), while others will have more perceptions from otolith afferents (i.e. tilt). In order to limit these side effects, the electrical current threshold will be adapted to each participant, and we will ask participants to perform the stimulation in a lighted room to enable them to have a visual fixation point, which will suppress the visual response. Finally, the Graybiel scale as well as visual analog scales for fatigue, well-being and pain will be used to quantify patients' feelings and perceived adverse effects.

## 11 SAFETY CONDUCTED AS CARE VIGILANCE

In accordance with the new research regulation involving the human person, there will be no collection of serious adverse events organized by the sponsor as part of the study.

However, as for all research involving the human person, the sponsor will transmit to the investigators concerned any information likely to affect the safety of persons (Art R1123-52

CSP) and will inform without delay the competent authority and the protection committee of new safety facts and, where appropriate, measures taken (Article R1123-59 of the CSP).

Nevertheless, health professionals are reminded that care vigilance applies, as a result any incident or adverse reaction suspected to be due to a drug or other health product as defined in Article L5311- 1 must be reported by the health professional to the vigilance networks (internet Portal for reporting adverse health events) who, after analysis, report them to the ANSM.

## 12 STATISTICAL CONSIDERATIONS

### 12.1 NUMBER OF SUBJECTS REQUIRED

The number of participants in this descriptive and exploratory study is not subject to power calculation. We plan to include 50 breast cancer patients, 25 treated with chemotherapy and 25 not treated with chemotherapy, as well as 25 healthy female volunteers (control group), for a total of 75 participants.

### 12.2 STATISTICAL ANALYSIS

**Axis 1:** In order to characterize the sleep of breast cancer patients before and after adjuvant chemotherapy, sleep parameters measured by polysomnography (in particular sleep efficiency and number of awakenings) or by questionnaire will be described in terms of headcount for qualitative variables, and mean and standard deviation (or median and range) for quantitative variables, at T1 and T2 in each of the groups of interest. Similarly, circadian rhythm parameters measured by actigraphy (e.g. mean amplitude over a week) or by salivary cortisol assay will be described at each time and by group. To assess the effect of cancer on sleep and circadian rhythm, parameters at T1 and T2 will be compared between patients and controls using a Chi test or a Student (or Wilcoxon) test. To assess the effect of chemotherapy on sleep and circadian rhythm, the parameters of chemotherapy-treated patients will be compared between T1 and T2 by a McNemar test or a Student (or Wilcoxon) test for paired series. Alternatively, the effect of chemotherapy on T2 parameters can be tested in linear or logistic models adjusted for T1 parameters. Relationships between sleep parameters and circadian rhythm parameters will be assessed using a correlation matrix (Pearson's or Spearman's). The relationship between sleep parameters and scores on cognitive tests and quality-of-life assessments can be assessed at any time using a linear mixed model (taking into account correlation between repeated measures of the same subject).

**Axis 2:** In order to assess the effect of galvanic vestibular stimulation on circadian rhythms, the evolution of circadian rhythm parameters measured by actigraphy during the 2-week intervention (in particular the amplitude and phase of the activity-rest rhythm) will be described by a linear mixed model. The model will include a time effect, an intervention effect (GVS or SHAM) and a time x intervention interaction (parameter of interest to assess whether GVS has an effect on the evolution of circadian rhythm compared with SHAM), and will be adjusted for group (patients or controls) and possibly treatment (chemotherapy or not). To meet secondary objectives, sleep parameters, cortisol levels, cognitive abilities and quality of life assessments will be described before (T2) and after intervention (T3) in each group of patients (GVS or SHAM) and controls (GVS only) and compared pre-post GVS by a McNemar test or a Student (or Wilcoxon) test for paired series. Alternatively, the effect of GVS on sleep, cognitive ability

and quality of life at T3 could be tested in linear or logistic models adjusted for parameters at T2.

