These studies have shown changes in the sleep's macrostructure in patients treated for breast cancer, but they have several limitations that prevent a precise understanding of the impact of cancer and treatment on sleep. The absence of a control group in several of these studies is the main limitation. Indeed, the presence of a control group with no history of cancer and a group without treatment makes it possible to determine whether changes in sleep architecture are secondary to the cancer itself or to treatment. In addition, the inclusion of heterogeneous populations in terms of age and cancer type may have limited the statistical power of the studies' results, and prevented changes in sleep architecture from being revealed. In addition, no studies have assessed changes in sleep patterns prior to initiation of chemotherapy. PSG also provides detailed information on the macro- and micro-structure of sleep, enabling links to be made with cognitive performance and the detection of potential sleep disorders such as apnea. New studies, more homogeneous in terms of eligibility criteria, but also longitudinal, are needed to determine the presence of sleep disorders in breast cancer patients. A better understanding of these sleep disturbances will also enable to determine their possible contribution to the onset of cognitive and psychopathological deficits.

Patients with breast cancer suffer not only from impaired episodic memory, but also from impaired executive functions. The latter are particularly involved in a particular form of episodic memory, spatial memory, which has so far received little attention in breast cancer. This type of memory enables to remember a route or find objects in different places, and is therefore essential for everyday life. What's more, it relies on the integrity of the hippocampus, a region that appears to be affected in women with breast cancer . Sleep disturbances are also known to impair executive functions involving the prefrontal cortex  and the cognitive control mechanisms that depend on it. These cognitive control mechanisms enable the regulation of behavior in complex situations, particularly after a stressful event. In breast cancer, sleep disorders could have a negative impact on these control mechanisms, leading to reduced resistance to stress.

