#### 5.4 MAIN OBJECTIVE

The project has two main aims, each with its own main objective.

**Axis 1:** To characterize the sleep of patients undergoing breast cancer treatment before and after adjuvant chemotherapy, compared with patients not treated with chemotherapy and with women free from history of cancer.

**Axis 2:** To explore the regulatory effect of galvanic vestibular stimulation (GVS) on circadian rhythms in patients undergoing treatment for localized breast cancer, compared with SHAM stimulation (not effective).

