## 6 RESEARCH HYPOTHESIS AND EXPECTED RESULTS

##### Axis 1:

- 1)
  - a) Sleep and circadian rhythms would be altered in patients before chemotherapy compared with cancer-free subjects. Chemotherapy would exacerbate these effects compared with the no-chemotherapy group
    - For sleep, more awakenings lasting more than a minute and poorer sleep quality are expected.

- For circadian rhythms, the sleep/wake and cortisol rhythms are expected to be less ample.
- b) Altered rhythms have deleterious effects on sleep quality**
- 2)** Cognitive abilities would be more impaired after than before chemotherapy, whereas no decline is expected in patients not treated with chemotherapy and in healthy subjects. More specifically, this decline is expected to affect:
    - Spatial and episodic memory
    - Working memory
    - Executive and attentional functions
    - Functional connectivity during the ANT (Attentional Network Test) task, particularly within the orientation and cognitive control networks
  - 3)** After chemotherapy, the cortical structure should be altered, particularly in the regions involved in the above-mentioned cognitive abilities (i.e., hippocampus, frontal regions, cerebellum) compared to before chemotherapy, and compared to patients not treated with chemotherapy and healthy subjects.
  - 4)** For both groups of patients, the dynamics of functional connectivity at rest prior to chemotherapy should be altered, with greater ruminations than in the healthy group.
  - 5) a)** Sleep disturbances (independently of the effects of anxiety and depression) are thought to be linked to cognitive abilities and their neuro-anatomical correlates, specifically:
    - Episodic and spatial memory performance
    - White matter structure and functional connectivity
  - b)** Sleep disturbances are also associated with hyperactivity of physiological stress systems
  - c)** Sleep disturbances are associated with a lower quality of life

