## 8 STUDY PLAN

### 8.1 METHODOLOGY

The ICANSLEEP project is a bicentric longitudinal study.

Data from 25 patients with localized breast cancer treated with chemotherapy will be compared with those from a group of 25 patients not treated with chemotherapy and a group of 25 cancer-free volunteers (control groups), matched for sex, age and years of education (Barbizet scale).

The various evaluations will be carried out as follows:

- At T1: Approximately 1.5 months after surgery and before the start of chemotherapy in the CHI group and before the start of radiotherapy in the NCH group,
- At T2: after a delay of around 6 months, within 2 weeks of the end of chemotherapy for the CHI group, or at a distance from radiotherapy for the NCH group,
- At T3: after a two-week intervention with GVS versus non-effective stimulation (known as SHAM). To assess the effect of GVS, patients will be assigned to either the effective GVS group or the SHAM group (random selection). SHAM stimulation involves using the device but receiving a very low-frequency current that has no effect on the vestibular system. This approach has already been used and validated in the COMETE unit (Caen, [name]) with which we collaborate. All cancer-free volunteer participants will undergo GVS.

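### Section 12.2 puts an uncontrolled before-after test in chemotherapy patients first for the chemotherapy effect, and leaves the comparison with patients not given chemotherapy as an optional model with no comparator named

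*Protocol*

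**What the plan says.** The question is set up as a between-group comparison in four places in the protocol:

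- **Section 5.4, Axis 1 main objective:** sleep is to be characterised "before and after adjuvant chemotherapy, compared with patients not treated with chemotherapy and with women free from history of cancer".
- **Section 6, hypothesis 1a:** "Chemotherapy would exacerbate these effects compared with the no-chemotherapy group".
- **Section 8.1:** data from the 25 patients "treated with chemotherapy will be compared with those from a group of 25 patients not treated with chemotherapy" and with 25 cancer-free volunteers.
- **Section 5.1:** having a cancer-free group and a group without treatment "makes it possible to determine whether changes in sleep architecture are secondary to the cancer itself or to treatment". Of earlier work, the same section says "The absence of a control group in several of these studies is the main limitation".

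Section 12.2, Axis 1, then deals with the patients not given chemotherapy (NCH) as follows:

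- Sleep parameters are described "at T1 and T2 in each of the groups of interest", which includes NCH.
- For the effect of cancer, patients are tested against controls. NCH presumably belongs to the patients here.
- For the effect of chemotherapy, "the parameters of chemotherapy-treated patients will be compared between T1 and T2 by a McNemar test or a Student (or Wilcoxon) test" for paired series. Only the chemotherapy group (CHI) enters this test.
- The next sentence adds: "Alternatively, the effect of chemotherapy on T2 parameters can be tested in linear or logistic models adjusted for T1 parameters". It names no comparison group, and nothing in the section says which of the two analyses leads.

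**The concern.** A paired test within CHI asks whether sleep changed between T1 and T2. Hypothesis 1a asks whether it changed more with chemotherapy than without. The two answers coincide only if nothing except chemotherapy moves the measurements over those months.

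The protocol itself gives grounds to doubt that. Section 5.1 discusses an earlier polysomnography result in which patients slept more after chemotherapy than before, and offers stress from the diagnosis and apprehension of chemotherapy at baseline as one explanation. In this study T1 falls about 1.5 months after surgery (section 8.1). Entry also requires a sleep complaint, ISI above 7 (section 8.3.1), so some regression to the mean is to be expected. It would act directly on the ISI and, on other sleep measures, only as far as they correlate with it.

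Both mechanisms would tend to improve sleep from T1 to T2. They could hide the harm that the study expects to see, and drift in the other direction could imitate it. The two analyses in section 12.2 also estimate different quantities, change over time in CHI and difference between CHI and NCH, so they can disagree.

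**Working it through.** **No figure in the plan to reproduce.** Section 12.1 states that the sample size rests on no power calculation. The protocol gives no alpha, effect size, SD or drift. What follows illustrates the mechanism.

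**Input from the protocol:** 25 patients in CHI and 25 in NCH (sections 8.1 and 12.1).

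**Assumptions, not in the protocol:** two-sided 5% test, no dropout, no chemotherapy effect, and a T1-T2 drift of d SDs of the change score.

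**Step 1. Rejection rate of the paired test within CHI.** The statistic follows a noncentral t distribution with n − 1 = 24 degrees of freedom and noncentrality d√n = 5d. The critical value is 2.064. The rejection rate is P(|T| > 2.064).

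| Drift d (SD of change) | Noncentrality 5d | Rejection rate |
|---|---|---|
| 0 | 0 | 5.0% |
| 0.1 | 0.5 | 7.7% |
| 0.2 | 1.0 | 16.1% |
| 0.3 | 1.5 | 30.2% |
| 0.5 | 2.5 | 67.0% |

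**Step 2. The same with drift in SDs of the measurement.** If T1 and T2 have equal SD and correlation ρ, the change score has SD √(2(1 − ρ)) in units of that SD. That is 1.18, 1.00 and 0.77 for ρ = 0.3, 0.5 and 0.7. A drift of 0.2 SD then gives 13% to 24% rejections over that range of ρ, 0.3 SD gives 23% to 46%, and 0.5 SD gives 53% to 87%.

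**Step 3. The controlled analysis under the same drift.** A linear model of T2 on T1 and group, 25 CHI against 25 NCH, was simulated 20,000 times for each combination of ρ (0.3, 0.5, 0.7) and drift (0.2, 0.3, 0.5 SD). The rejection rate lay between 4.9% and 5.2% throughout. This holds because the simulation gives both groups the same drift.

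**Step 4. What the controlled analysis costs in precision.** In SD units the standard error of the paired mean change is √(2(1 − ρ)/25). That of the T1-adjusted contrast is about √(2(1 − ρ²)/25). The ratio is √(1 + ρ): 1.14, 1.22 and 1.30 for ρ = 0.3, 0.5 and 0.7. The difference detectable with 80% power (normal approximation) is (1.96 + 0.84) × √(2/25) × √(1 − ρ²), or about 0.76, 0.69 and 0.57 SD.

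**The case against.** **NCH is not left out.** A reader might infer that the effect is tested in CHI alone and that NCH is never used. The protocol does not support that. A T1-adjusted model can estimate a chemotherapy effect only if patients without chemotherapy are in it, so the alternative implicitly uses NCH. NCH is also described at both times. This stands and limits the point to the order of the analyses and the missing comparator.

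**The main objective is to characterise.** Description by group answers that, and the disputed test serves secondary objective 1a. This is fair in part. Yet hypothesis 1a, which belongs to that objective, is worded against the no-chemotherapy group, and the main objective carries the same comparison.

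**The study calls itself descriptive and exploratory.** Section 12.1 says so, and no alpha or decision rule is fixed. This lowers the stakes. It does not make a before-after change within CHI an estimate of the chemotherapy effect.

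**A statistical analysis plan may settle which model leads.** It may. One might infer that the choice will be made after the data are seen, but the protocol does not say so. The point concerns the rule that the protocol states first.

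**The drift is assumed, and may not be shared.** The protocol gives no drift size. The explanation in section 5.1 includes apprehension of chemotherapy, which NCH would not share, and it names a rival: fatigue and sleep deprivation built up during treatment. Seasonal and first-night effects are not documented, and nothing here rests on them. Comparison with NCH removes only the shared part of any drift.

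**The contrast has its own confounding.** The groups are not randomised. T2 is two weeks after the last chemotherapy session in CHI but six months after T1 in NCH (section 8.4.4). NCH patients receive radiotherapy between the two assessments (section 8.1). All of this stands and must be stated with the result, but it gives no reason to put an analysis without any comparator first.

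**Conclusion.** The point holds in a limited form. The first-named test of the chemotherapy effect is an uncontrolled comparison that cannot answer hypothesis 1a. The analysis that could answer it is optional and names no comparator. This is a mismatch between a stated analysis and the protocol's own question, and it should be fixed. Because the study is exploratory, and the alternative model is at least mentioned, it does not undermine the whole design.

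The size cannot be read from the protocol. Rejection rates of about 8% to 67% apply to drifts of 0.1 to 0.5 SD of the change score, with 25 patients, a two-sided 5% test and no chemotherapy effect. They show how sensitive the paired test is and do not forecast this study's error rate. The 5% rate of the controlled model depends on CHI and NCH sharing the drift.

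**What to change.** In section 12.2, Axis 1:

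1. For each main criterion (sleep efficiency and number of awakenings), make a model of the T2 value on the T1 value and group the stated analysis.
2. Name NCH as the comparator, and report the CHI-NCH contrast with its 95% CI as the estimate of the chemotherapy effect.
3. Keep T1-T2 changes within each group as description, and delete the sentence that offers the model as an alternative.
4. State the limits of the contrast: no randomisation, different anchoring of T2 in the two groups, and radiotherapy in NCH.

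The change takes one paragraph and uses data already to be collected. The price is a wider interval than the paired one, by about 14% to 30% for T1-T2 correlations of 0.3 to 0.7 under the assumptions above, together with the residual confounding in item 4.

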## 4 SUMMARY OF TESTS TO BE PERFORMED

**Table 1** Summary of assessments offered to participants at different stages of the study

| Assessments                                                                                                                                                                                                                                                                                             | Time | Inclusion | T1
Within one month of inclusion and before the start of treatment (chemotherapy or radiotherapy) | T2
6 months after T1 | T3
2 weeks after T2 |
|---------------------------------------------------------------------------------------------------------------------------------------------------------------------------------------------------------------------------------------------------------------------------------------------------------|------|-----------|------------------------------------------------------------------------------------------------------|-------------------------|------------------------|
| Signature of informed consent                                                                                                                                                                                                                                                                           |      | •         |                                                                                                      |                         |                        |
| Sleep complaints and sleep apnea (questionnaires) :
- ISI
- Berlin Questionnaire                                                                                                                                                                                                                  |      | •         |                                                                                                      |                         |                        |
| Quality and physiology of sleep and circadian rhythms
- Questionnaires (home): ISI, PSQI, Horne and Ostberg
- Actigraphy and sleep diary (over the 2 weeks preceding each evaluation period T1, T2 and T3)
- Polysomnography
- Diurnal salivary cortisol
- CAR and cortisol pre-post MRI |      |           | •                                                                                                    | •                       | •                      |

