## **7 JUDGING CRITERIA**

### **7.1 MAIN CRITERION**

**Axis 1:** The primary endpoint is sleep efficiency (ratio of total sleep time to time spent in bed) and the number of awakenings lasting more than one minute. These data are derived from polysomnography.

**Axis 2:** The main criterion selected are amplitude (corresponding to half the maximum variation in the rhythm under consideration) and acrophase (i.e. the time of day when activity or cortisol is highest). Changes in sleep/wake rhythms will be quantified over the 2-week

intervention period, and will be derived from actigraphy. Changes in cortisol rhythm will be measured using saliva samples obtained at T2 and T3.

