#### **8.4.2 Study evaluations**

A table summarizing the investigations requested and a diagram showing the different stages in the evaluation of participants are included at the beginning of the document (*Figure 1*).

The first evaluation will be carried out within one month of inclusion and before the start of chemotherapy (CHI group) or radiotherapy (NCH group), depending on the availability of participants.

Throughout the evaluation sessions, participants will be accompanied by the UMR 1077 team, comprising a neuropsychologist, a sleep technician and a PhD student.

Prior to the assessment sessions, actigraphy data will be collected from participants 2 weeks before each assessment session (T1, T2 and T3). For this purpose, an actigraph and a sleep diary with explanations on how to use them will be provided to participants either *in person*, or remotely (actigraph and sleep diary sent by post and videoconference).

The assessments proposed to the participants during the different study phases (T1, T2 and T3) are presented in the following figures (*Figure 2* and *Figure 3*). Each evaluation sequence will be carried out over 2 half-days (afternoon and morning), separated by a night's sleep to allow polysomnography examination.

[figure not shown]

**Figure 2.** Assessments offered to participants at T1 and T2

**Note.** Actigraphy will be provided 2 weeks before T1, idem at T2; At T1, a preliminary interview will take place at the reception of the participants (approximately 30 min, in addition to the MRI instructions); At T1, a period of familiarization with the galvanic vestibular stimulation equipment will take place before the MRI examination (20 min); PSG:

[figure not shown]

**Figure 3.** Assessments offered to participants at T3

**Note.** Actigraphy will be provided 2 weeks before T3; PSG: Polysomnography

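### The Axis 2 main model leaves out the actigraphy recorded before T2, and its named test cannot see a GVS effect that is complete from the first sessions

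*Protocol*

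**What the plan says.** Section 12.2 (Axis 2) applies a linear mixed model to "the evolution of circadian rhythm parameters measured by actigraphy during the 2-week intervention". "The model will include a time effect, an intervention effect (GVS or SHAM) and a time x intervention interaction". The interaction is the "parameter of interest to assess whether GVS has an effect on the evolution of circadian rhythm compared with SHAM". The model "will be adjusted for group (patients or controls) and possibly treatment (chemotherapy or not"; no pre-stimulation rhythm value is listed.

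Section 7.1 sets the same window for the actigraphy part of the criterion: "Changes in sleep/wake rhythms will be quantified over the 2-week" intervention period. The cortisol part of the same criterion does have a before-and-after reference: "Changes in cortisol rhythm will be measured using saliva samples obtained at T2 and T3".

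Actigraphy is nevertheless recorded before stimulation starts. Table 1 in section 4 lists "Actigraphy and sleep diary (over the 2 weeks preceding each evaluation period T1, T2 and T3", and section 8.4.2 says that "actigraphy data will be collected from participants 2 weeks before each assessment session (T1, T2 and T3". Section 9.1.2 repeats this and names amplitude and acrophase as the main parameters. Section 10.1 hands out the headset at T2, so the pre-T2 fortnight precedes the stimulation programme.

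**The concern.** An interaction with time asks whether the two arms drift apart during the stimulation weeks. It does not ask whether they differ. If GVS moves amplitude or acrophase in the first few sessions and the change then holds, the arms run parallel from the start of the window and the named test has nothing to find.

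The intervention main effect would carry such a shift, but it is not the term the protocol singles out. Without the pre-T2 recording, it also mixes a real early effect with any chance difference between the arms in their usual rhythm. With only 50 randomised patients, that chance difference can be sizeable. At stake is a real early effect being reported as no effect on the main Axis 2 criterion, although the data that would reveal it have been collected.

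**Working it through.** **Figures in the plan.** Section 12.1 states that there is no power calculation, and no effect size, SD or alpha is given, so there is no figure to reproduce. Everything numerical below except the zero in step 1 rests on assumptions.

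**Inputs.** From the protocol: 14 days of actigraphy before T2 and 14 days during stimulation (sections 4, 8.4.2 and 8.4.5), and 50 patients randomised to GVS or SHAM (sections 8.1 and 12.1). Assumed: 25 per arm (the ratio is not stated); SD 1.0 between women, 0.5 between periods within a woman (applied to both periods) and 0.8 day to day; effect 0.5; two-sided 5%.

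**Step 1: an effect complete from day 1.** The arm difference is the same constant on every stimulation day. It does not depend on time, so the expected interaction is 0 whether time is a continuous day number, a factor for day or two weekly values (the protocol does not say which). Power equals the type I error, whatever the variances.

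**Step 2: an effect complete by day k.** Let the effect on day t be min(t/k, 1) of its full size. The fitted slope is Σ(t − 7.5)·e(t) / 227.5, where 227.5 = Σ(t − 7.5)² over 14 days. Multiplied by 13, it gives the share of the full effect seen as change from day 1 to day 14:

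| Complete by day | Share seen by slope | Share seen by mean |
|---|---|---|
| 1 | 0% | 100% |
| 2 | 19% | 96% |
| 3 | 35% | 93% |
| 5 | 63% | 86% |
| 7 | 83% | 79% |
| 14 | 93% | 54% |

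**Step 3: standard errors of the arm difference.**
- Variance of a woman's 14-day mean: 1.0² + 0.5² + 0.8²/14 = 1.296. Correlation of pre-T2 and stimulation means: 1/1.296 = 0.77.
- Unadjusted mean: √(1.296 × 2/25) = 0.322.
- Mean adjusted for pre-T2: √(1.296 × (1 − 0.772²) × 2/25) = 0.205.
- Slope per day: √(0.64/227.5 × 2/25) = 0.0150.

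**Step 4: power.**
- Step of 0.5. Slope: 0/0.0150 = 0, power 5%. Unadjusted mean: 0.5/0.322 = 1.55, about 33%. Adjusted mean: 0.5/0.205 = 2.44, about 67%. Simulation gives about 5%, 32% and 65%.
- Ramp reaching 0.5 on day 14. Slope: (0.5/14)/0.0150 = 2.38, about 65%. Adjusted mean: 0.5 × 7.5/14 = 0.268, and 0.268/0.205 = 1.31, about 25%. Simulation gives about 64% and 24%.

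**Step 5: how far the gain depends on the assumptions.** The unadjusted SE of a mean difference is 1/√(1 − r²) times the adjusted one: 1.15 at r = 0.5, 1.40 at r = 0.7 and 2.29 at r = 0.9. For an effect of 0.5 SD of the period mean, power rises from 42% to 53%, 70% and 98% respectively. Across six other variance settings (daily values with SD about 1), conditioning on the pre-T2 days cut the SE of the arm difference in level on the first stimulation day from 0.22–0.26 to 0.11–0.19. The SE of the slope itself hardly moved (for example 0.190 v 0.189). A longitudinal model that used the pre-T2 days and fitted a ramp starting from baseline had 68–99% power, against 56–77% for the planned slope.

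**The case against.** The strongest defence is that the slope test matches the stated hypothesis. Section 6 expects the sleep/wake rhythm to be strengthened progressively over the stimulation period. Sessions are repeated five times a week, and a full effect after one or two of them is a scenario the protocol does not put forward. This stands as a reason to keep the interaction. It is not a reason to leave the baseline out: the Axis 2 objective in section 5.4 is the regulatory effect of GVS compared with SHAM, not only its growth, and the progressive wording attaches most clearly to amplitude and less clearly to acrophase.

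A second defence is that the study is exploratory, and that section 12.2 offers T3 models adjusted for T2. Table 2 lists amplitude and acrophase under Axis 2 secondary objectives, so a generous reading might extend those models to actigraphy. But section 12.2 offers them only as an alternative, and for sleep, cognition and quality of life. The main model has its data window and its tested term fixed in the protocol, so this is not detail left to a later plan.

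A third point stands as a limit on the remedy. A common baseline mean across arms is justified only by randomisation, and section 8.1 gives GVS to every control. In the chemotherapy group the pre-T2 fortnight also lies close to the end of treatment, so its correlation with the following weeks is uncertain.

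**Conclusion.** The point holds in a limited form. As section 12.2 is written, the designated Axis 2 test has zero expected value for an effect that is complete from the first sessions and persists. Pre-T2 data that would allow a baseline-corrected comparison are collected but not used. The zero follows from the model. The size of the gain does not: 65% against 5% (slope) or 32% (unadjusted mean) under a step rests on the assumed SDs, an effect of 0.5 and 1:1 allocation.

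Three stronger readings are tempting and unsupported:
- A reader might infer that the plan detects only effects that keep growing for all 14 days. It does not: the slope captures about 63% of an effect complete by day 5 and 83% of one complete by day 7.
- A reader might infer that the baseline-adjusted mean is better throughout and should replace the slope. Under a ramp reaching 0.5 on day 14 it has about 24% power against 64%, so replacing the slope would weaken the analysis under the protocol's own hypothesis.
- A reader might infer that the slope is estimated less precisely without the baseline. Its SE is almost unchanged; the loss concerns the level.

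The change is worth making because it costs little and covers a pattern that the present test cannot see.

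**What to change.** In section 12.2, Axis 2, add the pre-T2 actigraphy days to the linear mixed model, either as a baseline period with a common mean across the randomised arms or as a covariate. Among the randomised patients, report two contrasts for amplitude and acrophase: the baseline-adjusted GVS-SHAM difference over the intervention period, and the time x intervention interaction, which is kept and not demoted. Leave the controls, who all receive GVS, out of the baseline-adjusted contrast. Align the wording in section 7.1 so that the actigraphy criterion names its pre-stimulation reference, as the cortisol part already does.

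The cost is a sentence or two and no new data. The downside is a second reported contrast, which has to be read alongside the first: the mean contrast alone is the weaker of the two when the effect builds gradually.
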